## 2.2 BACKGROUND

**Following evidence-based guideline recommendations for ADHD, including timely titration, use of structured reports and appropriate follow-up, may improve care.** The 2019 AAP Clinical Practice Guidelines for the management of ADHD state that stimulant medications can be effectively titrated on a 7-day basis.

Additionally, the AAP recommends that symptoms and impairment should be documented through structured reports. Adhering to follow-up recommendations and higher numbers of structured reports from teachers in the first year of treatment has been shown to significantly predict greater decreases in patient total symptom scores. Similarly, the Multimodal Treatment Study of Children With ADHD found that rapidly titrated medication dosing and close communication between the clinician and the child's teacher yielded improved outcomes over usual care.

**With the steadily progressive nature of academic activity and social skills expected during the elementary school years, any delays in improving symptoms will potentially have substantial negative long-term impact.**

The recommendations to advance stimulant therapy weekly, once the decision has been made to initiate it, are to support the most rapid, safe improvement in symptoms in order to optimize academic and social development opportunities. Delays in symptom control, once a diagnosis has been made, only serve to delay improvements in educational and social functioning. However, once optimal symptom control is achieved, children are still delayed in attaining milestones and may remain educationally and socially delayed even as they make improvement. As these educational and social skills are continuously progressing during these years, delays in improved functioning have long-term impact.

A frequently used method of gathering symptom information from different settings is the Vanderbilt Assessment. The Vanderbilt Assessment is a well-validated instrument that includes 18 questions on a 0-3 Likert scale regarding inattention and hyperactivity, as well as additional sections for screening for anxiety and depression. Versions are available for parent and teacher completion, for use during the diagnostic phase and subsequent management of ADHD. It is widely used as it is free of charge to providers and easy to score. (Appendix 1). Caregivers typically complete paper versions. This can be done in the office or at home, and returned at the subsequent in-office visit to the provider. In some cases, the teacher version is given to the caregiver to give to the child's primary teacher. The teacher completes the assessment, returns it to the caregiver (typically through the child's backpack), and the caregiver returns it to the provider at the next appointment. Alternatively, some practices allow teachers to fax it directly back to the practice, for matching in the office to the appropriate child. This cycle should repeat until the child's symptoms reach a substantially improved level. With the multitude of steps involved in this process, it is no surprise that the use of structured reports at follow-up is only 10%.

**Unfortunately, physicians encounter challenges in following these ADHD guidelines, particularly obtaining structured reports of symptoms (such as Vanderbilt Assessments), optimizing the timing of visits, and titrating quickly to optimal symptom control.** Furthermore, children with ADHD in rural areas encounter specific challenges to receiving this guideline-recommended care. They are more likely to suffer from challenges with access to primary care and specialty care, including behavioral health. Children in rural areas are less likely to receive the diagnosis of ADHD or stimulant treatment than those in urban areas. In the United States, primary care providers such as pediatricians and family medicine providers provide most ADHD care. Despite clear recommendations to use structured reports such as a Vanderbilt Assessment at diagnosis and follow-up, Epstein *et al.* found that the use of structured reports at the time of diagnosis in community practices was around 50% and use at follow-up was as low as 10%. As we review the traditional steps in obtaining these reports from caregivers and teachers, it is clear that there is an important unmet gap for children in rural settings, that if addressed, could substantially impact outcomes.

**Remote patient monitoring is a form of telehealth that involves the collection and transmission of health data from a patient to their health care team using digital health technologies.** It has been shown to be successful in a wide variety of pediatric conditions, including those gathering subjective data (such as pain) as well as objective data (such as glucose). While remote monitoring of ADHD is not well-studied, the use of electronic tools such as portals have been shown to improve some ADHD-care quality measures and resulted in improved outcomes including reductions in parent-rated ADHD symptoms as compared to usual care in urban settings. The use of these EMR-embedded tools has been studied in large networks with single-EMR clinical systems, and non-EMR-based portals have been studied in urban and suburban community practices that were linked. Providers in rural practices may encounter challenges with EMR-embedded tools because they have varied, office-based, electronic medical record vendors with less pediatric focus due to practice size. Additionally, providers in rural practices may lack the information technology (IT) infrastructure associated with large academic centers to create pediatric disease-specific tools.

**The need for improving ADHD care is universal; however, the translation of solutions that have worked in urban environments is not known for patients in rural environments.** Delivery of health services to pediatric patient homes using variable modalities of telehealth including remote patient monitoring has been widely recommended across various disease states. The RAMP will be a **non-EMR** based program that delivers text-message RAMP Report requests to caregivers and teachers and compiles patient data in provider dashboards. It eliminates the multiple handoffs of paper symptom assessment forms between caregivers, teachers and providers. Data is managed in Research Electronic Data Capture (REDCap), a secure web platform for building and managing online databases and surveys. The RAMP is being adapted from an existing program used successfully for behavioral health screening for pregnant women. The program was created at the Medical University of South Carolina and replicated at University of Mississippi Medical Center. Neither institution has a financial interest in the system and there is no intention to commercialize. This program has screened close to 400 women and has shown superior clinical outcomes compared to usual care. A non-EMR based platform will allow for evaluation of this approach across rural sites, without requiring significant IT investments, and eliminating the impact of the variability of EMRs across rural practices. Finally, a text-based platform to deliver

asynchronous care is in line with the most current user preferences for phone-based services, representing next-generation patient engagement.

**The research questions for the pilot project are as follows: First, is the use of RAMP acceptable to caregivers and teachers living in rural communities? Second, will providers of ADHD care in rural and underserved communities engage with dashboards collecting the RAMP Reports from caregivers and teachers?**

## 2.3 RISK/BENEFIT ASSESSMENT

### 2.3.1 KNOWN POTENTIAL RISKS

The study poses minimal risk to caregiver/child dyads. These dyads will provide protected health information (PHI) as well as ADHD symptoms. The RAMP will be housed on a secure platform and sites will use secure email for written communication between participants when possible. While the study team will make every effort to store this electronic information in secure electronic databases, there remains a risk of accidental as well as mandated disclosure of PHI.

A secondary risk to participants would be if challenges are encountered while navigating a new technology in an untested environment. There is a risk that a caregiver could provide information that does not get reviewed in a timely fashion by a provider. To mitigate this, caregivers are instructed in the platform to reach out to their provider directly if there is a serious concern. This risk to participants is no greater than what would be incurred during routine ADHD management. Additionally, if a provider does not review a report, he or she will receive a reminder prompt after 24. There may be a delay in response to participants if elements of the technology are not clear. An orientation to the platform will be conducted at the start of the study with all providers that may interact with the platform. If there are any challenges encountered during the process, a member of the study team will be readily available to assist.

### 2.3.2 KNOWN POTENTIAL BENEFITS

Previous studies of similar programs have shown benefit to participants and providers but not in rural settings. If the intervention is successful, caregiver and child participants may experience a more rapid titration of medication to optimal dosing, increased communication with health care providers as well as with teachers, and faster referrals to additional services.

The control group will receive digital education handouts about age-appropriate pediatric health topics through email.

### 2.3.3 ASSESSMENT OF POTENTIAL RISKS AND BENEFITS

We do not anticipate significant health risks to participants and will make every effort to minimize the possible risks described in Section 2.3.1. The benefit of understanding the effect of a Remote ADHD Monitoring Program on improving care for children in rural areas outweighs the risks. Standards of medical care provided to child participants will not be altered based on participants' study-related activities.

### 3 OBJECTIVES AND ENDPOINTS

| Objective                                                                             | Endpoint                                                                                                                              | Justification                                                                                                                                                                                                                                                                                                                                                                                                   |
|---------------------------------------------------------------------------------------|---------------------------------------------------------------------------------------------------------------------------------------|-----------------------------------------------------------------------------------------------------------------------------------------------------------------------------------------------------------------------------------------------------------------------------------------------------------------------------------------------------------------------------------------------------------------|
| Primary                                                                               |                                                                                                                                       |                                                                                                                                                                                                                                                                                                                                                                                                                 |
| Evaluate completion of clinical assessments by caregivers and teachers. | Number of completed caregiver and teacher clinical assessments (RAMP Report or paper assessment) that are returned to provider | The level of ongoing caregiver and teacher engagement in each arm will be important for planning a full-scale trial. Absolute number will be used as this is what has been shown to improve ADHD symptom control.  Increasing communication between caregivers and providers is important in enhancing the care of individuals with ADHD and literature in this area in rural settings is lacking. |
| Secondary                                                                             |                                                                                                                                       |                                                                                                                                                                                                                                                                                                                                                                                                                 |
| Evaluate provider acceptability of the RAMP through utilization measures.      | Proportion of provider review surveys with at least one available RAMP Report where review is documented                              | Because improvement in care requires bi-directional communication, the review of newly available reports by the provider will be important to measure. While we anticipate that providers will find accessing this information easy and helpful, it may be difficult to incorporate into usual workflow.                                                                                                        |

## 4 STUDY DESIGN

### 4.1 OVERALL DESIGN

The design is a pilot study that tests the utilization of an ADHD monitoring platform in a rural setting. We will examine utilization from the caregiver, provider, and teacher perspectives. We hypothesize that this platform will facilitate information provision from families and teachers to health care providers and will be a useful and acceptable means of ADHD symptom monitoring.

The entire timeline will span 17 months with three phases. In the first phase of the study, the providers from the participating practices will receive ADHD Best Practices education and training in the portal use, and will be asked to provide informed consent. A member of the clinic staff (nurse, medical assistant or practice manager) will be identified as site champion. The site champion will facilitate communication between the site study team and the clinic staff. The second phase of the study will focus on child/caregiver and provider utilization. Providers will identify patients with a diagnosis of ADHD who are being started on stimulant medication to be contacted by study staff for enrollment. Research coordinators will discuss the study, perform eligibility screening and obtain consent (if deemed eligible by PI). The consented caregiver/child dyads will be randomized to intervention (requests to submit the RAMP Reports for 3 months) or control (usual care with attention control) groups. Families will be approached until 36 caregiver/child dyads are enrolled (only one child in a family may be enrolled). Each practice will have 6 weeks to enroll 9 participants. After the 6 weeks, practices with low enrollment will receive additional supports. Each week, progress to target will be evaluated to determine if any practice needs additional resources. If multiple practices do not meet enrollment goals, the study team may consider relaxing exclusion/widening inclusion criteria (ex. include patients undergoing re-titration, widen age criteria) and/or opening enrollment. Enrollment will be paused for 3 months from the last month of school to the start of the new school year (beginning of May to end of July). This will decrease the burden on practices and study staff during the time of the year with the fewest number of ADHD diagnoses. Once enrolled, caregiver/child participants will be randomized to either the intervention or control group and followed for approximately 3 months. Participants randomized to the intervention group will submit RAMP reports weekly for 4 weeks and then monthly for 2 months. Participants randomized to the control group will receive digital education handouts at the same frequency as the RAMP reports in the intervention arm. Research coordinators will periodically review the child participant's EMR and mark how many paper symptom assessments are returned while enrolled on the study for both groups. Research coordinators will also access the RAMP platform to log RAMP reports returned by caregivers/teachers, RAMP reports reviewed by providers, and provider survey results. All caregiver participants will complete a 90-day Vanderbilt Assessment as a retention measure (see section 1.2.1 for more details). This phase will continue until all 36 participants have completed their 3-month study period. In the third phase, the above endpoints will be calculated, the full-scale trial will be designed, and the findings presented in a manuscript.

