## 6 STUDY INTERVENTION

### 6.1 STUDY INTERVENTION(S) ADMINISTRATION

#### 6.1.1 STUDY INTERVENTION DESCRIPTION

**Research Coordinator Procedures:** A research coordinator will be identified at each of the participating ISPCTN sites to organize study procedures at the practices in their state. In the first phase, they will work with site champions at the practices to assist with scheduling the ADHD Best Practice education, RAMP platform orientations, and informed consent encounters for all providers who care for children with ADHD. In the second phase, they will describe the study to interested caregivers and complete enrollment and randomization procedures as well as complete periodic chart reviews and participate in study-related calls. Prior to the start of the first phase, they will receive training in obtaining informed consent if not experienced, given scripted language to use with families when describing the study and supporting caregivers and providers who have not completed or reviewed reports, respectively.

**Provider Training:** All providers who care for children with ADHD within the study practices will be offered ADHD Best Practice education and RAMP orientation as an introduction to the study. Providers will provide informed consent prior to the start of caregiver/child recruitment and enrollment. This will ensure that there is current knowledge of best practices for ADHD diagnosis and care available to all children receiving care for ADHD within this study. The project is not focused on provider training, as these are not new guidelines, but rather addresses other potential barriers that are unique to rural settings. In addition to this clinical training module, all providers will be required to complete training in the provider use of the RAMP platform.

**The RAMP Platform:** The technology platform used for this study will be an adaptation of an existing program used for behavioral health screening for pregnant women. This program has screened close to 400 women and has shown superior clinical outcomes compared to usual care. The RAMP will be housed in REDCap, a HIPAA-compliant data collection tool. The intervention cohort will be notified of their randomization assignment with a text message or email. They will receive text message requests to fill out the RAMP Reports below. Their responses will be compiled into a RAMP Report which will be available to the provider on their dashboard of enrolled participants.

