## 8 STUDY ASSESSMENTS AND PROCEDURES

### 8.1 EFFICACY ASSESSMENTS

#### PRIMARY OUTCOME MEASURES

##### **Objective 1 – Evaluate completion of clinical assessments by caregivers and teachers.**

The number of completed clinical assessments (either paper assessments [control] or RAMP Reports [intervention] that are returned to providers during the 3-month study period will be counted. Each RAMP Report will be documented in the RAMP platform including a timestamp of submission. Throughout the study period, the research coordinators will facilitate recruitment, randomization, support retention, and perform chart abstraction.

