**Engaging with the School Environment:** It is a guideline recommended practice for ADHD symptom information to be requested from teachers in addition to caregivers. Teachers of children receiving usual care will obtain/complete/return paper symptom assessments in the usual way (as directed by the caregiver). The study team will then use the clinic's medical record to document paper assessments returned by teachers for usual care. Teachers of children assigned to the RAMP intervention will receive instructions from caregivers on how to create a RAMP user account and complete RAMP Reports. The study team will provide caregivers with information packets to give to teachers assigned to the RAMP arm (one teacher per child). Information packets will include a brief description of the purpose of the study, FERPA authorization (to share information directly

with the study, see section 10.1.1.1 and 34 CFR 99.30), and a QR code with instructions to connect teachers with the RAMP platform. RAMP Report requests will be delivered to teachers by automated text message, and their reports will be completed directly in the RAMP system. The study team will use the RAMP system to document RAMP Reports returned by teachers. The ADHD symptom questions teachers will answer in the RAMP Report are consistent with standard practice, are identical to the caregiver RAMP Report, and will be used by participating providers for the child's ADHD care management. Teachers must provide a phone number capable of receiving text messages and an email address.

Teachers will not complete study assessments, and their impressions of child behavior contained in the paper assessments or RAMP Reports will not be recorded by the study team outside the medical record or RAMP platform. For these reasons, teachers will not be considered research participants. No direct contact is planned between the study team and teachers. Teachers will be directed to contact caregivers if they need assistance with the study. If a child's teacher does not want to use the RAMP platform, the child will not be disqualified from the study.

---

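### RAMP Reports are logged automatically, but paper forms count only if an unblinded coordinator finds them in the EMR, so forms received but not found understate mainly the control count

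*Protocol*

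**What the plan says.** Section 3 of the Protocol defines the primary endpoint as the number of completed caregiver and teacher clinical assessments, on either medium, that get back to the provider. The two media are counted by different routes.

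- **RAMP Reports.** Section 8.1: "Each RAMP Report will be documented in the RAMP platform including a timestamp of submission". Section 6.3 repeats that submissions are time-stamped in REDCap.
- **Paper forms.** Under section 4.1, coordinators go through each child's EMR from time to time and "mark how many paper symptom assessments are returned while enrolled on the study for both groups". For control-arm teachers, 10.1.1 says: "The study team will then use the clinic's medical record to document paper assessments returned by teachers for usual care". Section 6.1.1 has coordinators "complete periodic chart reviews and participate in study-related calls", with no interval fixed.
- **What may be abstracted.** The 1.3 footnote limits chart review to whether the form is present, when it was submitted and whether a provider reviewed it.
- **Who abstracts.** Under 6.2 the research coordinator makes the allocation from the list, and the trial is unblinded.
- **What is compared.** Section 9.4.2 sets control paper forms against intervention RAMP Reports, using Poisson regression and a difference in means with a 95% CI. Intervention-arm paper is counted separately and goes to a sensitivity analysis.

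Section 2.2 describes the usual path of paper. A form is typically "returned at the subsequent in-office visit to the provider", and some practices let teachers fax theirs, to be matched to the child in the office.

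**The concern.** One arm's outcome records itself. The other arm's outcome depends on a form being filed and then found. A form that was received but is not in the chart, or appears there only as a score in a visit note, was returned in the sense of the endpoint, yet a check for the form's presence can miss it. That error can only lower the count, and it falls on the control arm's sole form type.

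The hypothesis in 9.1 is that RAMP yields more assessments, so the error favours RAMP. Section 4.2 discusses one bias, extra provider outreach to controls, and accepts it because it runs towards a false negative. This one runs the other way and is not discussed. Section 3 also names engagement in each arm as an input to the full-scale trial, so an understated control rate would carry forward.

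**Working it through.** The protocol states no capture rate for paper and no expected control count, so there is no figure of its own to reproduce here. The direction follows from the text. The size below rests on assumptions.

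**Inputs from the protocol**
- RAMP requests: 4 weekly + 2 monthly = 6 per reporter; caregiver + teacher gives 12 per child (1.1, 6.1.1).
- Expected RAMP return rate: 52.7% (9.2). Expected RAMP mean = 12 × 0.527 = 6.324.

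**Assumptions**
- m = true mean number of paper forms per control child that reach the practice: 1 to 3.
- c = share of those forms that the chart review finds: 0.7 to 0.9.

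**Formulas**
- True difference = 6.324 − m
- Observed difference = 6.324 − m·c
- Overstatement = m(1 − c); relative overstatement = m(1 − c) / (6.324 − m)

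| m | True difference | c = 0.9 | c = 0.8 | c = 0.7 |
|---|---|---|---|---|
| 1 | 5.32 | 5.42 (+0.1, 1.9%) | 5.52 (+0.2, 3.8%) | 5.62 (+0.3, 5.6%) |
| 2 | 4.32 | 4.52 (+0.2, 4.6%) | 4.72 (+0.4, 9.3%) | 4.92 (+0.6, 13.9%) |
| 3 | 3.32 | 3.62 (+0.3, 9.0%) | 3.92 (+0.6, 18.1%) | 4.22 (+0.9, 27.1%) |

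**On the ratio scale** of the Poisson model, the observed RAMP:control ratio is the true ratio times 1/c: 1.11, 1.25 and 1.43 times for c = 0.9, 0.8 and 0.7, whatever the means.

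**If intervention paper were added to that arm's count.** Section 9.4.2 also says that counted reports include any clinical assessment. Suppose a share s of the intervention arm's reports is on paper and is lost at the same rate. The inflation factor becomes (1 − s + s·c)/c. At c = 0.8 this is 1.25 for s = 0, 1.225 for s = 0.1 and 1.20 for s = 0.2. The bias shrinks a little and keeps its direction.

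**A low anchor.** Sections 2.2 cite about 10% use of structured reports at follow-up in community practice. Applied purely as an illustration to 12 opportunities, that gives m = 1.2 and a true difference of 5.12. The overstatement is then 0.12 to 0.36 forms, or 2% to 7%.

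**The case against.** Several points against this carry weight.

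- **Not every lost form counts.** A reader might infer that any paper loss biases the comparison. It does not. A form that disappears in a backpack never reached the provider; it is a true non-return and part of the barrier that RAMP is meant to remove. Only forms received but not found matter.
- **Not only the control arm.** Sections 4.1 and 6.2 have paper noted in both groups. Missed paper in the intervention arm mostly affects the separate count and the sensitivity analysis, so the error is mainly in the control arm, not exclusively.
- **The mechanism is inferred.** Nowhere does the protocol say that forms go unfiled or are kept only as scores, or that the four practices run different EMRs. Section 2.2 speaks of rural practices in general, and 5.1 requires only that each practice use an EMR and be willing to use the Vanderbilt as its main tool. Recording whether a form is present also leaves an unblinded coordinator little to judge.
- **Detail may sit elsewhere.** The MOP, data management plan and site procedures are not shown and may contain abstraction rules. The 1.3 footnote, however, is in the protocol and limits what those rules can draw on.
- **The top figure is a corner.** The 27% needs both the highest assumed control mean and the lowest assumed capture.

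A reader might also infer a high risk of a falsely significant result. In a simulation with 18 per arm, equal true means of 3 and c = 0.8, the two-sided 5% Poisson test rejects in about 19% of runs. That needs equal true means, whereas the protocol's own figures put RAMP well ahead, so it does not describe the expected trial.

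What stands is the unequal capture, its direction, and the absence in the protocol of a rule for what counts as a returned paper form or of any cross-check.

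**Conclusion.** The point holds in this limited form. Paper forms that reach the practice but are not filed or not found are missed mainly in the control arm. This understates the control count and overstates the RAMP-minus-control difference. With 70–90% capture, 1–3 true control forms per child and a RAMP mean of 6.3, the overstatement is about 0.1–0.9 forms, roughly 2–27%. Capture rate and control mean are both assumptions, and the low anchor points to the lower part of that range. RAMP stays ahead in every scenario tabulated, so the documents do not support saying that the direction of the result is in doubt. What is at risk is the size of the difference and the control-arm return rate carried into the full-scale trial. It is a cheap improvement worth making, not a flaw that invalidates the pilot.

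**What to change.** 1. In 4.1 and 8.1, count a paper assessment as returned, in either arm, if the chart shows the form itself, a recorded score, or a note that a completed form was received. Align the 1.3 footnote with this rule.
2. With the Day-90 study assessment, ask caregivers in both arms one identical question: how many paper symptom forms they and the teacher gave to the clinic, not counting the study assessment. Do not ask at the 1-week, 4-week or 2-month contacts, because repeated questions could prompt controls to return forms and so change the usual-care comparator.
3. Keep the EMR count as primary. Report the difference again with EMR-or-caregiver counts, as a sensitivity analysis and not as a bound on the truth.

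The cost is one question at a planned contact, one CRF field, one table and a small footnote edit that needs IRB review, since the change log shows the footnote was added to meet an IRB contingency. No extra visits or staff are needed, and the sample size and primary model do not change. The limits are caregiver recall error, caregivers' incomplete knowledge of forms that teachers fax directly, and no caregiver count for dyads who do not return the Day-90 assessment.
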